##### Plan for Missing Data

Several strategies will be deployed to accommodate the possibility that missing data will occur. This protocol will perform both per-protocol and ITT analyses; thus, we will follow all randomized participants regardless of the treatment received [52]. Our primary analysis is valid under the assumption that missing data are missing completely at random, using the Little missing completely at random test [53]. We will evaluate the plausibility of this assumption by determining the extent and pattern of missing data and using logistic regression to identify factors associated with dropout [54]. Sensitivity analysis will be performed under the assumption of missing not at random using a selection model, pattern mixture model, or semiparametric methods [55] to examine the robustness of conclusions from the primary analysis.

##### Minimizing Contamination Across Groups

Contamination will be minimized in several ways: (1) only individuals enrolled in the project will be provided with a single-use code to access the app; (2) couples and housemates will be randomized together; and (3) participants will be assessed at follow-up about their observation of others using the app. We will disguise these questions by asking (1) “Have you seen a different version of the app?”; (2) “Do you have a buddy who is also in the study but uses a different version of the app?”; and (3) “Did you find how different is your app from others?”

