##### Procedures

After meeting eligibility, participants will provide written consent and complete a baseline assessment. Participants will then be randomized (1:1) to either JomPrEP or TAU. Participants in both groups will have JomPrEP installed on their phones and be guided through its use. However, participants in the TAU group will receive JomPrEP with major intervention features inactivated. They will have access to only the resources center with information on HIV testing and PrEP, mental health, and addiction support services, and the chat function to contact the research staff. The research staff will assist in downloading the app and provide a tutorial on how to use the app.

Participants in the JomPrEP group will be provided with full app access, including a customizable page (*visual representation using avatars and pseudonyms*); visual dashboard (*tracking PrEP adherence, daily mood tracker*); HIV testing plan (*ordering self-testing kits, testing site locator*); PrEP Care Plan (*PrEPxpress—HIV risk assessment, scheduling and managing appointments, e-consult, an electronic script for PrEP medicine, discrete door-to-door delivery, accessing test results*); mental health support (*screening for psychiatric and substance use disorder, referral to mental health support services*), chat function (*ability to chat with clinical and research staff*); tailored notifications (*automated reminders for follow-up care*); and resources center (*multimedia library on information and resources on HIV testing, PrEP, risks, relationships, and psychiatric and substance use disorder*). The research staff will use an onboarding checklist to orient participants to download JomPrEP and its use. Participants will be encouraged to explore and use all components of JomPrEP. Participants can earn points for completing specific tasks on JomPrEP (ie, gamification) and personalize the frequency, timing, and content for reminder notifications and follow-up PrEP services. They can also contact the research or clinical staff using the chat function for support. Anyone identified at baseline who seroconverts during the study period will be referred to appropriate HIV treatment services.

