The framework for testing the study hypotheses will compare the differences between the 2 groups (JomPrEP vs TAU) over time. To test our primary hypotheses on binary outcomes of HIV testing and PrEP uptake, a generalized linear mixed model [50] with random subject effects will be built to account for the correlation in repeated measurements within participants. Treatment assignment, time, the interaction between time and treatment assignment, and any other hypothesized confounders will be included as covariates. HIV testing and PrEP uptake proportion at the 9-month follow-up will be estimated and compared using a linear contrast statement in SAS PROC GLIMMIX. Similar analyses will be conducted for the secondary binary outcomes: optimal adherence and PrEP persistence. As an alternative analytical plan for assessing the impact of the 2 groups on adherence to PrEP, continuous adherence variables will be analyzed using a linear mixed model [50] with the same set of covariates as the binary adherence outcome and percent changes in adherence between the different assessment points will be estimated and compared between the 2 arms using the linear contrast statement in SAS PROC MIXED. For the aforementioned model, the covariance structure will be selected based on the fit statistics (eg, Akaike information criterion and the Bayesian information criterion) [51]. Given the several strategies by which PrEP adherence will be measured, we will utilize Spearman correlation coefficients and scatterplots to assess the associations between the biomedical measure (dried blood spot) [45-48] and self-report measure (Visual Analog Scale) [49].

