##### Sample Size

We calculated the sample size based on the difference we expect in the primary outcome (ie, PrEP uptake) by month 9. A sample size of 121 per group achieves 90% power to detect a 10% increase in PrEP uptake for the JomPrEP group compared with the TAU group, assuming 50% PrEP uptake in the TAU group at the 1-sided .05 significance level. A sample of 268 participants will be enrolled and randomized to the JomPrEP and TAU groups to accommodate a 10% dropout. Assuming 60% of PrEP uptake in the JomPrEP group, this sample size provides 85% power in detecting a standardized effect size of 0.5 for the secondary outcomes of adherence and persistence.

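### Couples and housemates are allocated as units, but the primary model accounts only for correlation within a participant; if linked participants enrol, the one-sided .05 test is anti-conservative to that extent

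*Protocol article*

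**What the plan says.** Three parts of the protocol article bear on this.

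- **Allocation.** Under Minimizing Contamination Across Groups, one of the measures is that "couples and housemates will be randomized together". The Procedures section describes allocation of individuals and mentions no other unit: "Participants will then be randomized (1:1) to either JomPrEP or TAU".
- **Analysis.** For the two binary primary outcomes (HIV testing and PrEP uptake), the Analytical Plan says that "a generalized linear mixed model [50] with random subject effects will be built to account for the correlation in repeated measurements within participants". The fixed part is also listed: "Treatment assignment, time, the interaction between time and treatment assignment, and any other hypothesized confounders will be included as covariates". Month-9 proportions "will be estimated and compared using a linear contrast statement in SAS PROC GLIMMIX". For the covariance, "the covariance structure will be selected based on the fit statistics", with no level above the participant named. The secondary binary outcomes get similar analyses, continuous adherence a linear mixed model, and persistence also a Cox model; none of these mentions couples or households.
- **Sample size.** "A sample size of 121 per group achieves 90% power to detect a 10% increase in PrEP uptake", "assuming 50% PrEP uptake in the TAU group at the 1-sided .05 significance level". The only allowance added is 10% for dropout, giving 268 enrolled.

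**The concern.** Two men allocated as a unit always land in the same arm. If their outcomes are positively correlated, their covariance adds to the variance of the difference between arms. A random subject effect absorbs correlation between visits of one man; it cannot absorb correlation between two men. A model of that form treats the pair as two independent observations.

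Positive correlation is plausible. Partners and housemates can be expected to share decisions on testing and PrEP, and the contamination rule itself presumes that such men influence one another. At stake are the error rate of the efficacy test, which is already one-sided at .05, and the width of the confidence intervals. The same gap carries over to the secondary analyses.

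**Working it through.** **Inputs from the document.** 121 evaluable per group, 242 in total; one-sided .05; 50% uptake under TAU against 60% under JomPrEP; 10% dropout; couples and housemates allocated together; random effects at subject level only.

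**Inputs assumed, because the document gives neither.** f, the share of participants enrolled in linked pairs, and ICC, the correlation of the outcome within a pair.

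**The plan's own figure.** The standard two-proportion formula with 50% against 60%, one-sided .05 and 90% power gives 423 per group, not 121; with 121 per group the power is 46.7%. Clustering does not cause that gap, and it is a separate matter. It is noted here only because 242 is the base for the effective sample sizes below.

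**Step 1, design effect.** Take an arm of n men with outcome variance s², of whom f·n are in pairs, so f·n/2 pairs. The variance of the arm total is n·s² + (f·n/2)·2·ICC·s² = n·s²·(1 + f·ICC). For pairs, therefore, DE = 1 + f·ICC. For units of size m it is 1 + f·(m − 1)·ICC.

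**Step 2, actual error.** A test that ignores the pairs uses a standard error too small by the factor 1/√DE. Its actual one-sided error is 1 − Φ(1.645/√DE).

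**Step 3, effective sample.** 242/DE.

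| f | ICC | DE | 1.645/√DE | Actual one-sided error | Effective N of 242 |
|---|---|---|---|---|---|
| 0 | any | 1.00 | 1.645 | 5.0% | 242 |
| 0.1 | 0.3 | 1.03 | 1.621 | 5.25% | 235 |
| 0.1 | 0.5 | 1.05 | 1.605 | 5.4% | 230 |
| 0.2 | 0.5 | 1.10 | 1.568 | 5.8% | 220 |
| 0.4 | 0.5 | 1.20 | 1.502 | 6.7% | 202 |
| 0.4 | 0.7 | 1.28 | 1.454 | 7.3% | 189 |

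Across this range the planned standard error is too small by 1.5% (1 − 1/√1.03) to 11.6% (1 − 1/√1.28). Larger households do worse at the same f and ICC: with units of three, f = 0.2 and ICC = 0.5, DE is 1.20 rather than 1.10.

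**Check by simulation.** A month-9 two-sample z test that ignored pairs, with pairs allocated as units, N = 242 and 40,000 runs per setting, rejected in about .051 to .052 of runs without clustering, .056 at f = 0.1 and ICC = 0.5, .059 at f = 0.2 and ICC = 0.5, and .071 at f = 0.5 and ICC = 0.5. The formula gives .054, .058 and .071 for the last three. The simulation did not fit the planned mixed model, so both sets of figures approximate the planned test.

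**The case against.** The strongest objection is about size. Recruitment, as described under Study Settings and Participants, reaches individuals through flyers, geosocial networking apps and Facebook; couples or households are not sought out, and every housemate must meet all eligibility criteria himself. Nothing in the document supports a paired share of 20% to 40%, and the ICC is equally unsourced. At f = 0.1 the excess error is well under one percentage point, and next to the sample-size discrepancy noted above this is a second-order problem. All of that stands. It rules out saying flatly that the test is anti-conservative; the statement has to be conditional on linked men enrolling.

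A second objection is that naming random subject effects does not exclude a further level, which a statistical analysis plan could add. This carries less weight. The article itself fixes the allocation rule, the random-effects structure and the purpose of that structure, and these do not match. An analysis plan that followed the article would carry the mismatch forward.

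A reader might also infer that a partner or housemate who joins later inherits a known allocation, so that concealment fails for him, and might then want such men left out of the primary analysis. The document does not support this. Its wording reads most naturally as joint allocation at one time, and it describes no later joiners. Excluding randomized men would also conflict with the intent-to-treat analysis that the article uses for efficacy.

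**Conclusion.** The mismatch is in the text: some participants are allocated in clusters, and the stated model has nothing for that level. The direction of the error follows if linked men enrol and their outcomes are positively correlated. Its size cannot be derived from the document. The 5.25% to 7.3% range for a nominal 5% test rests on assumed pairs, a paired share of 0.1 to 0.4 and an ICC of 0.3 to 0.7. At the low end the effect is minor, and with no linked participants or zero correlation it vanishes. Confidence is high on the direction and low on the size. The correction is still worth making in advance, because unit membership may not be recoverable once data collection is over.

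**What to change.** 1. Record a randomization-unit identifier at enrolment, with each single participant as a unit of one.
2. In the primary models, use cluster-robust variance at the unit level, or add a random intercept for the unit above the subject effect. Do the same in the secondary analyses, including the linear mixed model for adherence and the Cox model for persistence.
3. Reconcile Procedures with Minimizing Contamination Across Groups, so that both state the unit of randomization.
4. State an assumed linked share and ICC in the sample-size section. On the document's own 121 per group, DE = 1.03 to 1.28 would mean 125 to 155 per group (121 × 1.03 = 124.6; 121 × 1.28 = 154.9).

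The cost is one extra variable, one change to the model or variance statement, and slightly wider intervals. With few pairs, a unit variance component in a binary mixed model may be weakly estimated; robust variance then suffices. The number of units, 242 × (1 − f/2), would still be about 194 to 230 over f = 0.4 to 0.1, ample for a robust variance.

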#### Phase IIB: Explore Multilevel Implementation Factors

We will use the Consolidated Framework for Implementation Research (CFIR) to gather multilevel implementation factors. We selected CFIR because it provides a structured menu of constructs associated with effective implementation and can be used flexibly at any phase, and has been used to guide PrEP implementation in other settings [56-58]. It consists of 5 domains with 39 underlying constructs [56]. As recommended [56], we have identified 11 constructs based on the relevancy to our trial (Table 2).

**Table 2 table2:** Constructs of CFIR^a^ to explore multilevel implementation factors.

CFIR domains and constructs		Sample questions
**Intervention**		
	Relative advantage	How does the JomPrEP app compare with other alternatives?
	Adaptability	What changes will be needed for the JomPrEP app to work effectively?
	Design quality and packaging	What is your perception of bundling HIV and mental health support services in the JomPrEP app?
**Internal Context**		
	Structural characteristics	What kinds of infrastructure changes will be needed to accommodate the intervention?
	Readiness for implementation	What level of endorsement or support have you seen or heard from leaders?
**External Context**		
	Patient needs and resources	What barriers will the users face while participating in the JomPrEP intervention?
**Participants**		
	Knowledge and beliefs about the intervention	How do you feel about integrating the JomPrEP app into your clinical setting? Do you have any feelings of anticipation? Stress? Enthusiasm? Why?
	Self-efficacy	How confident do you think your colleagues feel about using the JomPrEP app?
**Process**		
	Planning	What have you done (or what do you plan to do) to implement the JomPrEP program?
	Engaging	What steps have been taken to encourage people to use the JomPrEP app?

^a^CFIR: Consolidated Framework for Implementation Research.

We will conduct FGs with participants randomized to the JomPrEP group (n=16-20) and stakeholders (eg, clinicians and administrative staff from NGOs, clinics, and hospitals; those who do and do not participate in the trial; n=16-20), where we will measure implementation and process measures, existing and potential barriers and facilitators, as well as identify available resources and key facilitating stakeholders. For stakeholders, we will have 2 groups of matched clinicians (who do and do not participate in the trial). Administrative personnel will include supervisory personnel at the clinics, hospitals, and NGOs. The same process will occur when we start, and then again at the end of the project, where we will share results and assess changes from the baseline. During the FG sessions, participants will be asked about the multilevel implementation factors based on the sample guide available elsewhere [59] (Table 2) but tailored for the Malaysian context.

### Ethics Approval

The institutional review board at the University of Connecticut approved this protocol (H22-0049) with an institutional reliance agreement with the University of Malaya. This study is registered at ClinicalTrials.gov (NCT05325476).

## Results

As of September 2022, we have completed phase I of the proposed study. Based on a series of formative work completed during this phase, we have developed a fully functional, clinic-integrated JomPrEP app [60], which is available to download for free on both iOS and Android platforms (Multimedia Appendix 1). JomPrEP provides a virtual platform for MSM in Malaysia to facilitate their engagement in HIV prevention in a fast and convenient manner. It offers a range of HIV prevention (ie, HIV testing and PrEP) and other support services (eg, referral to mental health services), including several on-demand features (Figure 2). We have also developed a web-based “JomPrEP Clinic Dashboard,” which will provide role-based access to clinical staff from affiliated clinics to facilitate patient care for JomPrEP app users. Without an electronic health record in the local setting, our JomPrEP Clinic Dashboard functions more like an electronic health record system.

**Figure 2 figure2:**
[figure not shown]
Features included in JomPrEP. PrEP: pre-exposure prophylaxis; P/SUD: psychiatric and substance use disorders.

Data from beta testing (phase IC) demonstrated JomPrEP to be highly feasible and acceptable for HIV prevention efforts among MSM in Malaysia. Based on participant feedback provided during beta testing exit interviews, we are currently optimizing the app and the research protocols for a large-scale efficacy trial (phase II), which will commence in January 2023. Data collection for phase II will be completed in Spring 2025, followed by data analysis.

## Discussion

### Expected Findings

In this study, we propose to develop and test the efficacy of a clinic-integrated app (ie, “JomPrEP”). JomPrEP will be designed to virtually deliver an integrated HIV prevention intervention that will promote HIV testing and linkage to PrEP. We hypothesize that JomPrEP will be significantly more effective in improving uptake of HIV testing and PrEP among MSM in Malaysia. We also anticipate that the results and qualitative feedback from participants and stakeholders will inform the refinement of JomPrEP for a future implementation trial.

JomPrEP will help to reduce some of the individual- (eg, lack of information, psychiatric and substance use disorder, negative experiences with clinicians, low perceived risk) and structural-level barriers (eg, long waits and multiple visits, stigma, and discrimination from physicians) to HIV testing and PrEP care in multiple ways, by (1) offering relevant information and resources on PrEP, HIV risk reduction, and psychiatric and substance use disorder support services; (2) incorporating on-demand features with real-time e-Counseling, tracking, and monitoring linked and integrated with clinical services within 1 platform to deliver seamless transition without any in-person interaction with the clinicians. This enhancement on the traditional O2O service delivery model ensures open and nonjudgmental virtual space for MSM to discuss various issues with the clinicians without fear of stigma and discrimination [30,31]; (3) decreasing long clinic wait times and reducing the number of clinical visits; and (4) collaborating with local clinics and other stakeholders to deliver seamless, integrated HIV prevention services care as well as to ensure sustainability and further expansion of JomPrEP. If successful, JomPrEP will be among the first clinic-integrated apps to deliver comprehensive HIV prevention services for MSM in LMICs, including Malaysia. Furthermore, the app could be an innovative platform to link online service utilization and subsequent offline clinical services uptake (eg, HIV treatment services, psychiatric care).

### Planned Next Step

As part of the next step, we propose to conduct a type I hybrid implementation science trial [39] that involves an assessment of the efficacy of JomPrEP while assessing contextual implementation factors to guide its future adoption and scale-up.

### Limitations

Threat to internal validity includes retention and differential loss to follow-up. We will utilize established procedures to increase compliance with follow-up assessments, including minimal wait time for follow-up appointments, reminder messages between visits and prior to follow-up surveys, and incentives for completing study activities. If a participant misses a follow-up assessment, research staff will make additional outreach to support engagement. Additional threats to internal validity are issues around quality assurance during data collection. Possible technological difficulties with the app and server are additional concerns.

In addition, a number of strategies will be in place during different stages of the project to ensure the sustainability and scalability of JomPrEP. First, as part of the JomPrEP development process, we used the user-centered design approach that incorporated individual preferences at the center of the app design and grounded on continuous and structured interaction with end users. Second, we propose to use the hybrid effectiveness-implementation design to gather information on its potential for implementation in real-world settings while testing JomPrEP. This will help to simultaneously answer many questions (eg, client-, clinicians-, and administrative-level factors) important for transitioning to app implementation in real-world settings more comprehensively, accurately, and certainly earlier. Third, as part of the planning process, we met with several key local stakeholders, yielding an in-depth understanding of capacities and priorities that helped shape this project. Many clinics (mostly private clinics) across Malaysia have signaled interest in incorporating JomPrEP into their clinical care. Importantly, we will work with the local stakeholder to identify an organization to take ownership of JomPrEP and use it as a tool for scaling-up PrEP uptake across Malaysia at the end of the grant cycle.

### Conclusions

Limited HIV prevention resources and entrenched stigma, discrimination, and criminalization of same-sex behavior and substance use hamper access to HIV prevention services in Malaysia. Introducing a new app-based platform to deliver holistic HIV prevention services represents a paradigm shift in HIV prevention because it can deliver effective prevention in a confidential, less stigmatizing, and convenient manner. If found efficacious, JomPrEP can be adapted for a range of health outcomes and health care services delivery in these populations and other LMICs.

## Appendix

Multimedia Appendix 1 JomPrEP app screenshots.

Multimedia Appendix 2 Peer review report by NCI-J - Center for Scientific Review Special Emphasis Panel - Mobile Health: Technology and Outcomes in Low and Middle Income Countries - (National Institutes of Health, USA).

